## Abstract

Fibromyalgia is a complex chronic disorder involving persistent widespread pain accompanied by functional limitations, cognitive impairments, and alterations in neural processing. Previous research indicates that exercise-based interventions can play a key role in alleviating symptom burden and enhancing physical performance; however, there is limited evidence regarding their impact on neurophysiological mechanisms. Creative dance, in combination with strength training, may stimulate both motor and cognitive systems, promoting brain plasticity and functional improvements. This study will analyze the effects of a six-week strength and creative dance program on physical fitness under single- and dual-task conditions in women with fibromyalgia and will explore the associated changes in brain electrical activity and autonomic modulation. Methods: This randomized controlled trial will be divided into an exercise group (*n* = 22) and a control group (*n* = 22). The 6-week supervised intervention consists of two 60-min sessions per week, combining strength exercises and creative dance. Primary outcomes include physical fitness tests (strength, mobility, balance, and agility gait test in single-task and dual-task), fibromyalgia symptoms, and quality of life. Secondary outcomes include changes in electroencephalography, heart rate variability, physical activity level, and fear of falling. Statistical analyses will compare within- and between-group differences using non-parametric tests and effect sizes. It is hypothesized that the intervention will improve physical fitness and dual-task performance, alongside increases in brain activity power. This study may provide insights into the neurophysiological mechanisms underlying the benefits of exercise benefits in fibromyalgia.

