#### 2.2.2. Recruitment

The sample size will be calculated based on one of the study’s primary outcomes, i.e., the impact of FM. Data from a previous study [22] that will be used as a reference evaluated the effects of a creative dance intervention on this outcome. In that study, the impact of FM was reduced by 1.16 points compared with the control group after six weeks of intervention.

According to the results obtained in the G*Power statistical power analysis software version 3.1.9.7 (Heinrich Heine University Düsseldorf, Düsseldorf, Germany), assuming an effect size of f(V) = 0.98, a power of 85%, and a significance level of 0.05, a sample size of 22 people per intervention group is estimated. However, considering an anticipated dropout rate of 10%, a total of 44 participants (22 per group) will be needed to observe a significant effect.

Therefore, the participants recruitment will take place between January and March 2026. Both groups will consist of women with FM (exercise group: *n* = 22; and control group: *n* = 22) recruited from different FM associations in the region of Extremadura.

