### 2.4. Clusters Randomization

The clusters in this study are FM associations from the region of Extremadura (Cáceres, Almendralejo, Hervás, and Olivenza) in Spain. Each association will be randomly assigned to either the intervention group, which will participate in a structured physical activity program, or to the control group. The allocation sequence for the associations will be created using a computer-generated random number system (Random Number Generator tool; Google, LLC., Mountain View, CA, USA). Simple randomization will be applied, with no stratification, given the small number of clusters. The sequence will be recorded in a password-protected Excel file. Personnel responsible for enrolling associations and implementing the intervention will remain blinded to the allocation sequence until each cluster is assigned. The principal investigator (IP) will provide the group assignment immediately prior to the start of the intervention for each association, ensuring allocation concealment.

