### 2.13. Data Analysis

The collected outcomes will be compiled in an anonymized database for statistical processing. Both descriptive statistics and inferential analyses will be conducted. Data analysis will be performed using the Statistical Package for the Social Sciences software (SPSS, version 25.0; IBM Corp., Armonk, NY, USA). The Shapiro–Wilk and Kolmogorov–Smirnov test will be used to assess the normality of all variables.

Furthermore, to explore the effect of physical exercise intervention, physical performance tests will be analyzed under both single task and dual-task conditions. Dual-task cost will be calculated to quantify the impact of performing a cognitive task on physical performance. Given the cluster-randomized design, changes over time and between-group differences were analyzed using linear mixed-effects models, accounting for the hierarchical structure of the data, with participants nested within fibromyalgia associations. Group (intervention vs. control), time, and their interaction (group × time) were included as fixed effects. Random intercepts were specified for associations and for participants, and random slopes were included when appropriate, assuming an unstructured covariance matrix. The normality of model residuals was visually assessed for all variables.

To quantify the degree of clustering, the intra-cluster correlation coefficient (ICC) will estimate from the variance components of the mixed-effects models, calculated as the ratio of between-association variance to total variance (between-association plus residual variance). This parameter will be used to evaluate the magnitude of within-association dependence and to confirm the appropriateness of the cluster-adjusted analytical approach.

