EEG measures were included as secondary, exploratory outcomes. Although an exploratory hypothesis regarding changes in beta power was formulated based on previous literature [57], EEG analyses were not designed as confirmatory and were conducted to generate mechanistic insights. To reduce the number of comparisons and improve statistical power, regions of interest (ROIs) were defined as a priori by grouping electrodes according to anatomical location: frontal (Fp1, Fp2, F3, F4, and Fz), central (C3, C4, and Cz), and parietal (P3, P4, and Pz). Mean spectral power was computed for each frequency band within each ROI by averaging across electrodes. For exploratory analyses, a 2 × 2 factorial design implemented within the EEGLAB STUDY framework was used to examine EEG data before and after the intervention in alpha and theta bands. Permutation-based statistical testing with 2000 iterations was applied, and multiple comparisons were controlled using the false-discovery rate (FDR) correction.

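### The only clustering term guaranteed in the mixed model cancels out of group × time, the term that matters is optional and undefined, and the ICC formula omits the participant variance

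*Protocol article*

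**What the plan says.** Section 2.4 makes the association the unit of randomisation: "Each association will be randomly assigned to either the intervention group, which will participate in a structured physical activity program, or to the control group". It names four: "The clusters in this study are FM associations from the region of Extremadura (Cáceres, Almendralejo, Hervás, and Olivenza) in Spain". Section 2.3 sets one baseline and one post-intervention assessment.

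Section 2.13 introduces linear mixed models because the design is cluster-randomised. Fixed effects are group, time and group × time. The random part reads: "Random intercepts were specified for associations and for participants, and random slopes were included when appropriate, assuming an unstructured covariance matrix". It does not say which unit the slopes belong to, or what makes them appropriate.

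The same section defines the ICC as association variance over total variance, "calculated as the ratio of between-association variance to total variance (between-association plus residual variance", and says that it will be used to confirm that the cluster-adjusted approach is appropriate. The Abstract describes a different analysis: "Statistical analyses will compare within- and between-group differences using non-parametric tests and effect sizes".

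**The concern.** Hypothesis H1 expects improvement relative to both baseline and control, and in this model that is most directly the group × time term. Group × time compares changes, so anything constant within an association over time is subtracted away. A difference between associations in how much their members change is not subtracted, and could arise from the trainer, the group or the local setting. If the model has no term for it, the standard error is too small and the false-positive rate exceeds 5%, although the report would describe the analysis as cluster-adjusted.

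The ICC is meant to support that description. It is computed with a denominator that is not the total variance of the fitted model, and it measures clustering of levels rather than of change.

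**Working it through.** **Inputs.** From the protocol article: four associations (section 2.4); 44 participants, 22 per group (section 2.2.2); two visits (section 2.3); the fixed and random effects and the ICC formula (section 2.13). Assumed, because the article gives no values: two associations per arm with 11 participants each (simple randomisation does not guarantee 2:2), complete data, the variance components, and an ICC of change from 0 to 0.10.

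**1. The plan's own sample size.** Section 2.2.2 states "assuming an effect size of f(V) = 0.98, a power of 85%, and a significance level of 0.05". Reading 0.98 as Cohen's d, a two-sided two-sample t-test needs 20 per group (power 85.5%), and 20 × 1.1 = 22. So 22 per group is reproduced as an individually randomised comparison, with no allowance for clustering. The f(V) label is a separate matter.

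**2. Cancellation.** For participant i in association j, change = (fixed time effects) + (post residual − pre residual). Both random intercepts subtract out. With residual variance 0.45:

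SE(group × time) = √[2 × 0.45 × (1/22 + 1/22)] = √0.0818 = 0.286.

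The generalised least squares SE, with participant variance 0.50, is 0.286 for association-intercept variances of 0, 0.05, 0.2, 1 and 10. The intercept has no influence on this test.

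**3. What an association slope would do.** With association-level variance τ for change and two associations per arm, the variance gains τ/2 + τ/2 = τ:

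| τ | SE = √(0.0818 + τ) |
|---|---|
| 0 | 0.286 |
| 0.02 | 0.319 |
| 0.05 | 0.363 |
| 0.10 | 0.426 |
| 0.20 | 0.531 |

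**4. Type I error if that slope is absent.** The test is then a change-score t-test on 44 − 2 = 42 df. The design effect is 1 + (11 − 1) × ICC of change. Simulated null trials at nominal 5%:

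| ICC of change | Design effect | Participant-level test | Cluster-level t-test, 2 df |
|---|---|---|---|
| 0 | 1.0 | 5% | 5% |
| 0.02 | 1.2 | 7% | 5% |
| 0.05 | 1.5 | 11% | 5% |
| 0.10 | 2.0 | 17% | 5% |

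**5. One data-driven reading of the optional slope.** Suppose the association slope is kept only when significant. It is kept in 14% of trials at ICC 0.05 and 25% at 0.10, and type I error remains 9.6% and 13.2%. Always fitting it, with 2 df whenever its variance estimate is positive, gives 5.3% and 6.5%.

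**6. The ICC formula.** As written it is A/(A + R). For the model as fitted it should be A/(A + P + R), where A is association, P participant and R residual variance:

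| A, P, R (assumed) | As written | Full variance |
|---|---|---|
| 0.05, 0.50, 0.45 | 0.05/0.50 = 0.10 | 0.05 |
| 0.05, 0.65, 0.30 | 0.05/0.35 = 0.14 | 0.05 |
| 0.05, 0.75, 0.20 | 0.05/0.25 = 0.20 | 0.05 |

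Both versions use the intercept variance, which step 2 shows has no bearing on group × time.

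**7. Power of a valid test.** For the cluster-level t-test with 4 − 2 = 2 df, the critical value is 4.303 and the non-centrality is 0.98/√[(2/22) × design effect]. At ICC 0 it is 3.25, with power 43%. At ICC 0.05 it is 2.65, with power about 33%. Both are without baseline adjustment.

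**The case against.** A reader might infer that the treatment test is simply not adjusted for clustering. The document does not support that. Section 2.13 allows random slopes, and an unstructured covariance has meaning only where an intercept and a slope share a level. With one value per visit and two visits, a participant slope cannot be separated from the residual, so an association slope for time is the natural reading, and it does enter the SE (step 3). This stands, and it makes the defect conditional. It does not remove it: no level or rule is stated, and an unstructured intercept–slope matrix asks for three parameters from four associations, so the slope could easily be dropped or estimated at zero.

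Nor does section 2.13 name group × time as the sole treatment test. A post-visit contrast from the same model keeps the association intercept. Its variance is (0.50 + 0.45) × (2/22) + A, so at A = 0.05 its SE is √0.136 = 0.369. That is correct, but the article does not designate that contrast either.

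A reader might also infer that a low ICC would be used to abandon the adjustment. Nothing says so: the mixed model follows from the design, and the ICC is only to confirm it. An overstated ICC would, if anything, favour keeping the adjustment. The denominator is therefore a reporting error that leaves the treatment test unchanged.

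Finally, an article may leave model detail to an analysis plan. That excuses brevity. It does not excuse an explicit formula that is wrong, or a claim of cluster adjustment that the guaranteed terms do not deliver for group × time.

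**Conclusion.** The point holds in conditional form. The cancellation is exact for complete pre/post data and approximate with unbalanced missing data. If no association-level slope is fitted, type I error for group × time is about 7%, 11% and 17% at ICC of change 0.02, 0.05 and 0.10. These values are assumptions, as are the 2:2 split and 11 per association. If the slope is always fitted with suitable degrees of freedom, the problem largely disappears, but the article does not commit to that.

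The ICC formula is wrong as written, irrespective of assumptions. The overstatement is two- to four-fold in the examples, and its size depends on the participant share. Even when corrected, it cannot confirm adjustment of a test on change.

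The Abstract's non-parametric tests do not match the mixed models of section 2.13, and the two need to be aligned.

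**What to change.** In section 2.13:

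- Name the treatment test. Either make association × time a mandatory random effect with between-cluster degrees of freedom (2), or analyse baseline-adjusted outcomes at association level with a 2-df t-test. The second is simpler and avoids a variance component that four associations may estimate at zero.
- State that this analysis is kept whatever the estimated ICC.
- Define ICC = association / (association + participant + residual) and report it descriptively.
- Bring the Abstract into line with section 2.13.

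The changes are to wording, but the cost is real. Confidence intervals widen, and power at d = 0.98 with four associations is about 43% at ICC 0 and 33% at ICC 0.05, before any gain from baseline adjustment. Section 2.2.2 says that "a total of 44 participants (22 per group) will be needed to observe a significant effect" on the basis of 85% power. That statement should be restated for the cluster-level test, because four associations are a design limit that no analysis wording can cure.

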**H1.** Six weeks of strength training and creative dance are expected to significantly improve physical fitness (strength, mobility, balance, functional capacity, and gait agility) in individuals with FM, under both single- and dual-task conditions, compared with their baseline status and a control group.**H2.** It is hypothesized, for exploratory purposes, that the physical exercise intervention will be associated with specific changes in resting-state brain electrical activity, characterized primarily by increased beta power, that could be related to increased cerebral blood flow [13]. Also, the autonomic modulation would be enhanced [18].

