### 2.12. Outcome

#### 2.12.1. Primary Outcomes Measures (Confirmatory Analyses)

(A)Questionnaires

Impact of the Disease

The FM Impact Questionnaire Revised (FIQR) [28] is a self-administered instrument composed of 21 items. Each item is rated on a 0–10 scale, with higher scores indicating greater disease impact. The questionnaire is structured into three domains: (a) function, (b) overall impact, and (c) symptoms. The total score, obtained by summing the three domains, ranges from 0 to 100, with higher values reflecting a greater overall impact of FM. In this study, the validated Spanish version of the FIQR [29] will be applied.

Health-Related Quality of Life

The EuroQol-5 dimensions 5 levels (EQ-5D-5L) measures health-related quality of life across five domains (mobility, self-care, usual activities, pain/discomfort, and anxiety/depression), each with five response levels. It also includes a visual analog scale ranging from 0 (worst health) to 100 (best health). The instrument has been validated in Spanish populations [30].

(B)Physical Fitness

Handgrip Strength

The Handgrip Strength (HGS) test will be used to assess maximal isometric hand strength. Participants will stand upright with their elbow extended at hip height and exert maximal force on a hand-held dynamometer (Takei TKK 5401, Takei Scientific Instruments Co., Ltd., Tokyo, Japan) featuring analog grip and adjustable handle to accommodate various hand sizes. Two repetitions will be performed for each hand, with a one-min rest interval between attempts. The highest value from each hand will be used for analysis [31].

Timed Up and Go

The Timed Up and Go (TUG) test is a dynamic test of mobility and balance in which participants rise from a chair without using their hands, walk 3 m as quickly as possible without running, turn around a cone, return to the chair, and sit down [32]. Performance is measured as the time taken to complete the task with ChronoJump software (version 2.2.0 Barcelona, Spain) and Chronopic hardware (DIN A-4, 210 × 297 mm), which will be placed on the backrest of the chair; one practice trial will be allowed for familiarization, after which the test will begin with the command “Ready, go”.

Short Physical Performance Battery

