The Agility Challenge for the Elderly (ACE) test will be used to assess performance under fall-threatening, real-life-like motor demands. The ACE consists of a standardized course set on a volleyball court, comprising three domains: stop and go, cutting maneuvers, and spatial orientation, each targeting a specific aspect of agility. Participants will complete four trials per session, interspersed with at least 3 min of rest; the first attempt on each testing day will serve as a familiarization trial. Instructions are to walk as fast as possible without running. Errors in the execution of the spatial orientation task (incorrect order) will be recorded. To avoid learning effects, cone numbers will be individually randomized for each trial. The ACE has demonstrated high reliability and validity in older adults [23].

Dual-Task Condition

Under dual-task conditions, participants will be required to execute a physical task (TUG, ACT, and CST) while concurrently engaging in a cognitive activity. The cognitive task will involve performing serial subtractions by two, starting from a randomly selected odd number greater than 100.

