In the event of participant attrition or missing data due to insufficient attendance, the analyses will follow an intention-to-treat approach, whereby all randomized participants will be included in the analysis according to their originally assigned group regardless of their level of adherence to the intervention. To address missing outcome data, an appropriate imputation strategy will be applied. Where necessary, missing outcome data will be handled using multiple imputations methods. This procedure will be performed following the assumptions for missing at random. When imputation is not feasible, the last observation carried forward or baseline-value carried forward strategies will be applied, depending on data characteristics. In addition, a per-protocol sensitivity analysis will be conducted including only participants who attend the majority of the scheduled sessions to evaluate the robustness of the findings and account for intervention dose–response effects.

The alpha level of significance (0.05) will be adjusted according to the Benjamini–Hochberg procedure to avoid type I error derived from multiple comparisons [55]. Effects sizes were computed and interpreted according to discipline-specific thresholds recommended for physiotherapy and rehabilitation research [56]. For measures of individual differences (Pearson’s r), effect sizes of 0.3, 0.5, and 0.6 were interpreted as small, medium, and large, respectively. For group differences (Cohen’s d or Hedges’ g), effect sizes of 0.1, 0.4, and 0.8 were considered small, medium, and large, respectively.

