### 4.3. Limitations

This study includes only women, which limits its generalizability to the broader FM population. The intervention period is relatively short, and there is no follow-up to assess the persistence of effects over time, which may not capture long-term adaptations. In addition, the control group will continue with usual care without monitoring physical activity levels, which may potentially attenuate between-group differences. Moreover, the absence of an active control group may introduce placebo effects, which cannot be fully ruled out and should be considered when interpreting the results. Finally, although adequately powered for the primary outcomes, the sample size remains modest for neurophysiological subgroup analyses, particularly the EEG subsample, which may limit the robustness and generalizability of these specific findings.

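### Eleven or twelve confirmatory primary tests share a Benjamini–Hochberg rule, but only FIQR was sized, at unadjusted 0.05, and FIQR is in neither H1 nor objective (a)

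*Protocol article*

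**What the plan says.** Protocol article, section 2.12.1, under a heading that opens "Primary Outcomes Measures (Confirmatory Analyses", lists FIQR, EQ-5D-5L, handgrip strength, TUG, SPPB, the 30 s chair stand (CST), the arm curl (ACT) and the ACE agility course. It adds a dual-task condition in which "participants will be required to execute a physical task (TUG, ACT, and CST) while concurrently engaging in a cognitive activity". Handgrip uses the best value from each hand. No instrument is singled out or ranked.

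Section 2.2.2 states: "The sample size will be calculated based on one of the study’s primary outcomes, i.e., the impact of FM". Its inputs are f(V) = 0.98, 85% power and a significance level of 0.05. The result is 22 per group, with a 10% dropout allowance. The instrument for FM impact is given in section 2.12.1: "The FM Impact Questionnaire Revised (FIQR) [28] is a self-administered instrument composed of 21 items".

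On multiplicity, section 2.13 states: "The alpha level of significance (0.05) will be adjusted according to the Benjamini–Hochberg procedure to avoid type I error derived from multiple comparisons".

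Objective (a) and H1, in the Introduction, concern physical fitness only: strength, mobility, balance, functional capacity and gait agility. H1 expects gains in these "under both single- and dual-task conditions, compared with their baseline status and a control group". Section 4.3 describes the trial, "although adequately powered for the primary outcomes", as modest in size only for the neurophysiological subgroup analyses.

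**The concern.** Four statements that should fit together do not.

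- The outcome that sets the sample size is not in the hypothesis.
- The hypothesis covers outcomes for which no power was calculated.
- The sizing uses 0.05, while the analysis will test at an adjusted level.
- The adjustment is said to guard against type I error across analyses labelled confirmatory, but the method chosen controls the expected share of false positives among the positives. It does not control the chance of any false positive.

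At stake is what a positive result would mean. With no single outcome carrying the conclusion, a significant result on any of eight instruments could be reported as confirmatory success. The reader would be told that the error rate and the power are those of one test at 0.05.

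**Working it through.** **Counting the tests.** Eight instruments + 3 dual-task versions (TUG, ACT, CST) = 11. A separate test for the second hand makes 12. Adding the EQ visual analogue scale (1) and dual-task costs (3) would make 16. The figures below use 12.

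**Reproducing the plan's size.** Take a two-sample t-test, two-sided 0.05, with 0.98 read as Cohen's d. The non-centrality is d × √(n/2).

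- n = 20 per arm: 0.98 × √10 = 3.10, power 85.5%. This is the smallest n that reaches 85%.
- Adding 10%: 20 × 1.1 = 22, the plan's figure.
- n = 22 per arm: 0.98 × √11 = 3.25, power 88.8%.

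Taken literally, f(V) = 0.98 needs only about 12 participants in total, which does not reproduce 22 per group. Reading 0.98 as d is an assumption, but it is the reading that fits the plan's number. With 10% dropout, 22 × 0.9 = 19.8, so about 20 per arm complete.

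**What Benjamini–Hochberg does to the FIQR test.** The ordered p-values p(1) ≤ … ≤ p(12) are compared with 0.05 × k/12, and all hypotheses up to the largest k that passes are rejected. The level at which FIQR is tested therefore depends on how many other outcomes respond. If none does, it is about 0.05/12 = 0.0042, and the t-test power at d = 0.98 is 58.9% (n = 22) or 52.7% (n = 20). The other rows come from simulating t-tests with d = 0.98 for each responding outcome and no clustering. Ranges run from correlation 0.5 to 0.

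| Outcomes that respond (of 12) | 22 per arm | 20 completers per arm |
|---|---|---|
| FIQR only | 59% | 53% |
| Six, including FIQR | 78–80% | 72–75% |
| All 12 | 85–88% | 81–84% |
| FIQR alone at unadjusted 0.05 | 89% | 85.5% |

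**What it does to the error rate.** In the same setting with 22 per arm, the chance of at least one false positive among the 12 is:

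- no outcome responds: 5.0% (independent), 4.1% (correlation 0.5);
- six respond: about 14% (independent), about 10% (correlation 0.5);
- three or nine respond (normal approximation): between 8% and 12%.

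The false discovery rate stays at or below 5% throughout. So the method does what it is designed to do, but that is not what section 2.13 says it is for.

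**Matching H1 to the tests.** TUG covers mobility and balance, and CST and ACT cover strength. All three have dual-task versions. Gait agility is measured by ACE and lower-body functional capacity by SPPB, and neither is among the dual-task tests in section 2.12.1.

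**The case against.** The strongest reply is that several primaries under a declared false discovery rate are a legitimate design, that the procedure is named and cited, and that no familywise rate is promised. The plan also expects broad benefit: H1 covers every fitness domain, and the Discussion anticipates gains in symptoms and quality of life. If all 12 outcomes respond, power is 85–88% with 22 per arm, close to the stated 85%. The exact family may be listed in an analysis plan that is not shown, and its absence is not held against the protocol here.

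Much of this stands, and it rules out some stronger readings:

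- A reader might infer that the stated power applies to no test as it will be performed. It does not follow, because power is roughly preserved if nearly all outcomes respond.
- A reader might infer that error is uncontrolled. It is not: when nothing responds, the chance of any false claim is 4–5%.
- A reader might infer that dual-task balance cannot be tested. Section 2.12.1 defines TUG as a test of mobility and balance, and TUG is done under dual task.
- The count of 12 depends on testing each hand. With 11 tests, power when only FIQR responds is 60% instead of 59%, which changes nothing of substance.
- If 0.98 really were f, the effect would be so large that adjustment would cost little power, but the plan's 22 per group would then be unexplained.

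The reply does not remove the conflict in the text. The plan names FDR control for its EEG analyses, but for outcomes it calls confirmatory it speaks of avoiding type I error. It sizes one outcome at a level it will not use, and then claims adequate power for the primary outcomes in the plural.

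**Conclusion.** The concern holds in this form: the confirmatory label, the multiplicity rule, the sized outcome and the hypothesis do not agree.

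- FIQR, the only sized outcome, is in neither objective (a) nor H1.
- Under the plan's own rule, FIQR power ranges from 59% to 85–88% with 22 per arm, and from 53% to 81–84% with 20 completers. The like-for-like unadjusted figures are 89% and 85.5%. The planned 85% is kept only if nearly all outcomes respond and few participants are lost.
- The chance of any false confirmatory claim is about 10–14% if half of 12 outcomes respond.
- The power claim in section 4.3 has no support for outcomes other than FIQR.
- H1's dual-task claim for ACE and SPPB has no test.

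These figures assume d = 0.98 for each responding outcome, two-sided t-tests, 12 tests and no clustering. Because whole associations are randomised, the power figures are optimistic and serve as illustration. The mismatch itself rests on the text alone.

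**What to change.** Name one primary outcome, tested at 0.05 on the group-by-time contrast. There are two routes:

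- FIQR total, which is already sized. Add it to objective (a) and H1. This shifts the stated question away from fitness.
- One fitness test from H1, with the power restated for that test. This keeps the stated question but needs a new calculation.

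Make the remaining outcomes secondary. Use Holm if confirmatory claims are wanted for them; otherwise keep Benjamini–Hochberg and describe it as false discovery rate control.

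If several primaries are kept, say that the false discovery rate is the target and give power under the adjusted rule as a range. For scale, 85% power at 0.05/12 would need 34 per arm, or 34/0.9 = 37.8, so 38 with dropout, still ignoring clustering.

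In either case, limit the power claim in section 4.3 to the sized outcome, and limit the dual-task part of H1 to TUG, ACT and CST.

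The cost is mainly wording, plus one power calculation on the second route. The other outcomes lose the primary label, and the registered record may need an update. Section 2.2.2 places recruitment in January to March 2026, so the change should be dated and made before outcome data are analysed.
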